#### Measurement-based integrated care

As part of MBIC, patients will meet with the DCM every 1–4 weeks, depending on their treatment plans, to complete brief psychotherapy interventions. Mental health measures and medication response and adherence will be collected using the iPad Depression Screening and Monitoring application and will be recorded in the EHR.

##### Follow-up visits

Patients will return to the clinic to complete all study measures and be compensated at the following time points: one-month post education session, six months post enrollment, and 12 months post enrollment. Between follow-up visits, research personnel will contact patients monthly to remind them of study participation and future appointments. If patients do not return for their follow-up visits, data will be collected from their medical record to include PHQ-9 scores and medication information, if available.

##### Intervention fidelity and data monitoring

Each research team member will undergo depression education training with the Principal Investigator and protocol and data collection training with the Project Coordinator. Research assistants will meet with the Principal Investigator and perform a final, practice education session prior to depression education intervention visits with participants. Additionally, education sessions will be audio recorded (with patients’ consent) and regularly reviewed by the Principal Investigator to assure adherence to the protocol. The Project Coordinator will perform data audits quarterly to assure data collection accuracy.

### Measures/Assessments

Demographic information will be collected from each participant to include gender, age, marital status, level of education, and co-morbid medical conditions (self-report). Three brief mental health measures will be collected via the iPad Depression Screening and Monitoring application technology by clinical staff and transferred to the research database by research staff. All research and clinical trial data will be collected via REDCap (Research Electronic Data Capture), a secure, web-based application used for a variety of research and maintained by Vanderbilt University Office of Research [43]. All measures have been validated in Spanish.

#### Patient Health Questionnaire-9 (PHQ-9)

The PHQ-9 is a self-report measure that assesses the frequency of symptoms on each of the nine DSM-IV [41] criteria for depression for “the last two weeks.” Responses for each item are scored as 0 for “not at all,” 1 for “several days,” 2 for “more than half the days,” and 3 for “nearly every day,” which results in a range of possible scores of 0–27. Total scores of 5–9 represent mild depression, 10–14 represent moderate depression, 15–19 represent moderately severe depression, and > 20 represent severe depression. Patients with a PHQ-9 score ≥ 10 are considered to have clinically significant depressive symptoms. The PHQ-9 has been shown to be a reliable and valid measure of depression severity in primary care samples with a Cronbach’s alpha of 0.89 and has demonstrated construct validity among African American, Hispanic, and non-Hispanic white populations [44, 45]. The PHQ-9 is designed to provide necessary information about potential depression diagnoses while not overburdening patients and providers. The PHQ-9 will be administered via the iPad screening and monitoring application at screening and all follow-up MBIC and research visits.

#### Generalized Anxiety Disorder-7 (GAD-7)

The GAD-7 is a seven-item self-report scale for identifying the presence of generalized anxiety disorder (GAD) and assessing symptom severity. The items of the GAD-7 are based on the diagnostic criteria for GAD in the DSM-IV and assess frequency of symptoms over the last two weeks using four response options: “not at all,” “several days,” “more than half the days,” and “nearly every day,” scored as 0, 1, 2, and 3, respectively. A score of 10 or greater on the GAD-7 represents a point for identifying cases of GAD. Cut points of 5, 10, and 15 represent mild, moderate, and severe levels of anxiety, respectively. The reliability of the GAD-7 in primary care settings, as well as in the general population, has demonstrated excellent internal consistency reliability with a Cronbach’s alpha of 0.92 and 0.89, respectively [40]. The GAD-7 will be administered after a positive screen for depression and at all follow-up visits. The GAD-7 will be administered via the iPad screening and monitoring application at screening at all follow-up MBIC and research visits.

#### Patient Adherence Questionnaire (PAQ)

The PAQ [46] is a two-item measure of adherence to antidepressant medication over the past week, possible changes in dose made by the patient without consultation with their provider, and reason for the change (sample response: “I reduced my dose because I felt better”). The PAQ is scored as 0 for one day or less of missing the medication, and 1 for days > 1 missed, and each reason endorsed for changes made in dose. Any score greater than ≥ 1 is considered “non-adherent to treatment” and will prompt the provider to address adherence. The PAQ will be administered via the iPad screening and monitoring application at all follow up MBIC and research visits for those patients who are prescribed medication.

#### Depression Knowledge Measure (DKM)

The DKM [32] is a 17-item measure that evaluates symptom recognition and treatment knowledge. Symptom recognition is assessed with a list of ten depression symptoms (sleeping too little, eating too much, feeling agitated, feeling guilty, and loss of interest) and five non-depressive symptoms (hearing voices, being full of energy, being violent, having hallucinations, and feeling confident). Scoring for this section allocates 1 point for each symptom that is correctly identified as a depression symptom or not a depression symptom. Treatment knowledge is measured with seven true–false questions from the Depression Literacy Questionnaire (D-Lit) measure adapted for use with Hispanic populations [13, 47]. The D-Lit has demonstrated internal consistency and test–retest reliability [47, 48] and has been used with immigrant populations [49]. Each correctly answered item is given a score of 1 point. With ten symptom recognition items and seven treatment knowledge items, the DKM scores range from 0 (all incorrect) to 17 (all correct). The measure will be administered at baseline, after the education session, at the one-month post-education session, and at the six-month and 12-month research follow-up visits.

Three brief stigma measures will be used to measure key stigma constructs that deter depression treatment utilization among the Hispanic population. These measures have demonstrated validity and reliability among Spanish-speaking, Hispanic primary care patients [50]. The three scales will be administered at baseline, after the education session, one-month post education session, and at the six-month and 12-month research follow-up visits.

#### Stigma Concerns about Mental Health Care (SCMHC)

The SCMHC [50] is a three-item measure that assesses stigma-related barriers to depression treatment utilization (sample item: “I would not want to receive treatment for depression because of being embarrassed to talk about personal matters with others”). Adapted from a larger measure of barriers to depression treatment [51, 52], response options are scored as 0 = “Disagree,” 1 = “Agree,” and 7 = “don’t know/refuse.” Scores for the measure are calculated by taking the sum of the three items (except for the items answered “don’t know/refuse”), with total score in the range of 0–3. The criterion-related and predictive validity of the three-item measure has been supported with a sample of Latinos diagnosed with depression and has demonstrated good internal consistency reliability with a Cronbach’s alpha of 0.84 [50].

#### Latino Scale for Antidepressant Stigma (LSAS)

The LSAS [50] is a seven-item measure designed to assess stigma specifically related to the use of antidepressant medications among Latinos. Respondents are asked to state how most people think with regard to stigma-related statements pertaining to use of antidepressants (sample item: “Prescription medicines for depression are for people who are not strong”). Possible response items are scored 0 = “No one thinks that way,” 1 = “Some people think that way,” 2 = “Everyone thinks that way,” and 7 = “Don’t know or refuse to answer.” The LSAS score is calculated by taking the sum of the seven items (except for the items answered as “don’t know or refuse to answer,” with total scores in the range of 0–14. LSAS scores have been correlated with depression treatment utilization and the scale has demonstrated good internal consistency reliability with a Cronbach’s alpha of 0.80 [50].

#### Social Distance (SD) scale

The SD is a six-item scale, which measures social distance desirability from someone with depression or history of depression treatment (sample item: “Would you be friends with someone who is or had been in treatment for depression?”) [53, 54]. Social distance is a widely measured stigma construct studied in mental health research [55]. Possible response items are scored 0 = “no,” 1 = “maybe,” 2 = “yes,” and 7 = “don’t know/refused.” Scores are calculated by taking the sum of items 1–6 (except for items answered with “don’t know/refuse”), with total scores in the range of 0–12. Lower scores indicate greater social distance. The relationship between SD scores and depression treatment engagement has been previously reported in a sample of Latinos with depression [50]. Previous studies have reported excellent internal consistency reliability with caregivers of patients with bipolar disorders [56]. The SD has demonstrated adequate internal consistency reliability with a Cronbach’s alpha of 0.75.

### Data analysis

#### Sample size

A total of 150 participants will be randomly assigned to the treatment and control groups. Intervention and control groups, estimated at 56 participants each, are required to have an 80% chance of detecting an effect size of 0.57 (power = 0.80) with a two-sided 5% significance level between the two group on depression scores. The effect size of 0.57 was calculated in a similar multisite randomized controlled trial of depression among women (N = 205) in an OB-GYN clinic with a similarly racially diverse, mixed socioeconomic status population [57]. Assuming an attrition rate of 25%, 70 participants for each group would be needed in the current study, which represents a cautious estimation. A systematic review of interventions to increase recovery from depression in primary care settings found attrition rates at the 12-month follow-up visit to be in the range of 6–18% [58].

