The primary outcome for Aim 2 is the change from baseline to 12-month scores on the PHQ-9 depression measure (dependent variable) for patients enrolled in MBIC. Outcomes will then be compared between and the MBIC + DEF and the MBIC + SE intervention groups.Current literature on the PHQ-9 suggests that a 5-point drop in mean depression scores is an indication of a clinically significant response to treatment [59]. The DEF group is hypothesized to have a greater proportion of the group report a clinically significant decrease in depression scores (5-point decrease in PHQ-9 scores) when compared with the SE group.The U.S. Department of Health and Human Services suggests that the objective of collaborative care research should be to have 40% or more of the patients realize a 50% or greater reduction in depression scores [60].

The evaluation of Aim 3 will examine the feasibility of universal screening for depression using the iPad Depression Screening and Monitoring technology, and will be measured by its positive predictive value, clinical utility, ease of use, and acceptability of routine use among clinicians:Quantify the number of adult patients screened per month and if the score is being placed in the EHR.Determine if the iPad Depression Screening application changes PCP approach to the diagnosis and treatment of depression as measured by the number of patients with a new depression diagnosis as a percentage of the total number of adult patients seen in the clinic compared to a matched set the year prior to the study based on EHR (baseline data).Quantify changes in the number of patients with a depression diagnosis being treated with antidepressants by the PCP as a percentage of the total number of patients seen in the clinic compared to a matched set the year prior to the study based on EHR (baseline data).

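### The sample-size figures do not reproduce: 56 per group gives about 85% power at 0.57 rather than 80%, and 70 per group does not keep 56 after 25% attrition; the planned 150 is unaffected

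*Protocol article*

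**What the plan says.** All of the calculation is in the Sample size section, under Data analysis.

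- Requirement before attrition: "Intervention and control groups, estimated at 56 participants each, are required to have an 80% chance of detecting an effect size of 0.57".
- Test level and outcome: "with a two-sided 5% significance level between the two group on depression scores".
- Allowance for loss: "Assuming an attrition rate of 25%, 70 participants for each group would be needed in the current study". The section calls this allowance cautious and compares it with 12-month attrition of 6–18% in a systematic review that it cites.
- Enrolment: "A total of 150 participants will be randomly assigned to the treatment and control groups". Setting and participants and Randomization give the same total.

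The effect size comes from one earlier randomized trial of depression among women. The Analysis section names the change in PHQ-9 score from baseline to 12 months as the Aim 2 primary outcome. Beneath it is a hypothesis about responders: "The DEF group is hypothesized to have a greater proportion of the group report a clinically significant decrease in depression scores", meaning a drop of 5 points.

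**The concern.** The section prints every input needed to recompute its result, and the result does not follow from them. The number called necessary for 80% power is too large for that power. The number called necessary after attrition is too small to preserve the first number. The text does not connect the resulting 140 with the 150 to be randomized.

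This paragraph is where a reader learns what difference the trial can detect and how much loss it can absorb. As printed, it misstates the required number, the power or effect size that goes with 56, and the attrition that 70 tolerates.

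**Working it through.** **Inputs from the Sample size section:** standardized difference d = 0.57 (so SD = 1), two-sided α = 0.05, power 0.80, 56 per group, 25% attrition, 70 per group after attrition, 150 randomized. Equal allocation (75 per group) is an assumption. The ratio is not given in words, but the Randomization section's 75 blocks for 150 participants imply blocks of two.

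**Step 1. Reproduce the 56.** For two means, n per group = 2(z₀.₉₇₅ + z_power)² / d².

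- 80% power: 2 × (1.960 + 0.842)² / 0.57² = 15.70 / 0.3249 = 48.3, so 49. The exact t-test gives 49.3, so **50**.
- 85% power: 56 by the same formula; the t-test gives 56.2.

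**Step 2. What 56 per group provides.**

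- Power at 0.57: Φ(0.57 × √(56/2) − 1.960) = Φ(1.056) = 85.5%. The t-test gives **84.8%**.
- Effect detectable with 80% power: 2.802 × √(2/56) = 0.529. The t-test gives **0.534**.

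**Step 3. Could another convention give 56 at 80% power?**

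| Variant | n per group |
|---|---|
| One-sided 5% | 39 |
| Two-sided α = 0.025 | 59 |
| Rank test, relative efficiency 0.955 | 49.3 / 0.955 = 51.6, so 52 |
| Rank test, worst-case efficiency 0.864 | 49.3 / 0.864 = 57.1 (48.3 / 0.864 = 55.9 from the normal formula) |

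Only the last comes close. The article mentions no rank test for the depression scores and plans a mixed-design ANOVA, so its text does not support that route.

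**Step 4. Attrition.** Keeping m completers when a fraction a is lost requires m / (1 − a).

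- Stated figure: 56 × 1.25 = 70, which reproduces the printed number by the wrong operation. It also equals 56 / 0.80, the figure for 20% loss.
- Correct figure: 56 / 0.75 = 74.7, so **75 per group, 150 in total**.
- Completers from 70 after 25% loss: 70 × 0.75 = **52.5**, which is 3.5 short of 56. Power at 0.57 with 52.5 per group is 82.5% by t-test (83.2% by the normal formula).
- Starting from the 50 that 80% power needs: 50 / 0.75 = 66.7, so 67 per group.

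**Step 5. The trial as planned.** 75 × 0.75 = 56.25 completers per group, giving 85.0% power at 0.57 by t-test.

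**The case against.** The strongest reply is that neither error harms the design. The first is conservative, since 56 exceeds 50. The second still leaves about 82% power, so 70 per group meets the 80% goal under 25% loss; indeed 67 would. At the worst attrition in the cited review, 18%, 70 would leave 70 × 0.82 = 57.4 and so keep the 56. All of this stands, and it limits the point to the accuracy of the text.

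Three stronger readings may tempt a reader, and the article does not support them.

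- *The section sets two incompatible targets, 140 and 150.* It gives 70 per group as a need and 150 as the number to be randomized. Enrolling more than a stated minimum is no contradiction, and 150 is used consistently elsewhere.
- *The trial lacks the power that it claims.* At an effect of 0.57 and 25% loss, 140 or 150 randomized would both exceed 80%. The article gives no basis for putting a smaller effect in place of 0.57.
- *The power statement is for the wrong outcome.* The section powers depression scores, the named Aim 2 primary outcome is the change in PHQ-9 score, and the Analysis section plans ANOVA for the outcome measures. These agree. The 5-point responder sentence is a hypothesis listed beneath that outcome, and nothing makes it the primary test. Its power would depend on response rates that the article does not give.

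**Conclusion.** Two figures are wrong as written. For the stated inputs, 80% power needs 50 per group; 56 corresponds to about 85% power at 0.57, or to 80% power at about 0.53. The article does not show whether the power or the effect size was misstated. The attrition step multiplies by 1.25 where it should divide by 0.75, so 70 falls 5 per group short of the 75 that would keep 56.

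The practical effect is small. Planned enrolment of 150 equals the correctly inflated number, and power on the PHQ-9 comparison stays above 80% at 0.57 with 25% loss. This is a minor text correction. It rests on a two-sample comparison of means, equal allocation, and the article's own effect size and attrition rate.

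**What to change.** The sponsor should first check the source calculation and confirm whether the power or the effect size behind 56 was misstated. The 70 should then be deleted and the statement reworded along these lines:

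> 75 per group are randomized; 25% attrition leaves 56 per group, giving about 85% power for a standardized difference of 0.57 (80% for 0.53) in PHQ-9 scores.

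If 80% power at 0.57 was intended throughout, the requirement is 50 per group, or 67 after 25% attrition, and the 150 planned exceeds it.

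Optionally, one sentence could say that this power applies to the continuous PHQ-9 change and not to the proportion with a 5-point drop. No responder power should be inserted on assumed rates.

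The cost is a few words of text. Enrolment, conduct and analysis do not change.

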#### Analysis

In addition to the study measures, additional data collected from the EHR will include demographics (age, marital status, race/ethnicity, insurance status) and medical co-morbidity. Planned data analyses include bivariate analyses of baseline data to compare demographic and clinical characteristics of the two intervention groups. In order to examine the success of randomization, t-tests and chi-square tests will be used to check for between-group equivalence. For each dependent variable, intent-to-treat longitudinal analyses will be conducted and outcomes for the two intervention groups will be compared. Mixed-design analysis of variance (repeated measures ANOVA with a between-subjects factor) tests will assess for within-group changes over time and for significant differences between the MBIC + DEF and MBIC + SE groups for each of the various outcome measures. Between-group differences in the likelihood in engagement in depression treatment (depression treatment and other treatment modalities) will be tested through chi-square tests followed by binary logistics regression modeling. Engagement in treatment will be dichotomously coded. All tests will be two-tailed with *p* < 0.05 used to determine significance. Study aims 1 and 2 will be tested for the MBIC + DEF versus MBIC + SE. All models will be checked for the need for additional covariates (demographic and clinical baseline characteristics) and interaction terms. Analyses will use all available data (i.e. intent-to-treat analyses) from participants with baseline data, post education (DEF or SE) visits and 12-month follow-up visits.

The evaluation of Aim 1 will examine the specific effects of the MBIC + DEF to increase knowledge about depression, reduce stigma, and increase engagement in depression treatment compared to MBIC + SE as measured by the following:Changes in knowledge of depression among Hispanic patients pre and post DEF compared with SE, as measured by the DKM. The DEF group is expected to report significantly greater DKM scores over time when compared with the SE group indicating gains in depression knowledge following receipt of depression education.Changes in attitudes among Hispanic patients toward depression pre and post DEF compared with SE using the SCMHC, LSAS, and the SD measures. The DEF group is expected to report significant changes in SCMHC, LSAS, and the SD over time when compared to the SE group and reported reductions in stigma related to mental health and psychiatric medications following depression education.Determine engagement in depression treatment for patients in DEF vs. SE.Quantify the number of patients diagnosed with depression and received the DEF intervention who went on to begin depression treatment compared with SE. The DEF group is hypothesized to have a greater portion of individuals engaging in depression treatment than the SE group following treatment. Furthermore, participants in the DEF group will have an increased likelihood of later engaging in treatment following the intervention.Quantify which treatment modality the patient with depression chose after the DEF compared to SE: pharmacotherapy; counseling; or other behavioral intervention. The DEF group is hypothesized to have a greater portion of individuals engaging in pharmacotherapy, counseling, or other behavioral interventions than the SE group following treatment. Furthermore, participants in the DEF group will have an increased likelihood of later engaging in pharmacotherapy, counseling, or other behavioral interventions following the depression.

The primary outcome for Aim 2 is the change from baseline to 12-month scores on the PHQ-9 depression measure (dependent variable) for patients enrolled in MBIC. Outcomes will then be compared between and the MBIC + DEF and the MBIC + SE intervention groups.Current literature on the PHQ-9 suggests that a 5-point drop in mean depression scores is an indication of a clinically significant response to treatment [59]. The DEF group is hypothesized to have a greater proportion of the group report a clinically significant decrease in depression scores (5-point decrease in PHQ-9 scores) when compared with the SE group.The U.S. Department of Health and Human Services suggests that the objective of collaborative care research should be to have 40% or more of the patients realize a 50% or greater reduction in depression scores [60].

The evaluation of Aim 3 will examine the feasibility of universal screening for depression using the iPad Depression Screening and Monitoring technology, and will be measured by its positive predictive value, clinical utility, ease of use, and acceptability of routine use among clinicians:Quantify the number of adult patients screened per month and if the score is being placed in the EHR.Determine if the iPad Depression Screening application changes PCP approach to the diagnosis and treatment of depression as measured by the number of patients with a new depression diagnosis as a percentage of the total number of adult patients seen in the clinic compared to a matched set the year prior to the study based on EHR (baseline data).Quantify changes in the number of patients with a depression diagnosis being treated with antidepressants by the PCP as a percentage of the total number of patients seen in the clinic compared to a matched set the year prior to the study based on EHR (baseline data).

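### The 12-month PHQ-9 change is assigned to mixed-design ANOVA with an open covariate set; a baseline-adjusted 12-month contrast has more power at no cost, and the stated 80% can, but need not, be missed without it

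*Protocol article*

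**What the plan says.** The Analysis section of the protocol article gives one method for each outcome measure: "Mixed-design analysis of variance (repeated measures ANOVA with a between-subjects factor) tests will assess for within-group changes over time and for significant differences between" the two arms. It then leaves the model open: "All models will be checked for the need for additional covariates (demographic and clinical baseline characteristics) and interaction terms". The same section plans t-tests and chi-square tests of baseline equivalence between the arms.

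For Aim 2 it states: "The primary outcome for Aim 2 is the change from baseline to 12-month scores on the PHQ-9 depression measure", to be compared between the arms. It adds a hypothesis about a proportion, defined by a 5-point drop: "The DEF group is hypothesized to have a greater proportion of the group report a clinically significant decrease in depression scores". A benchmark of a 50% reduction is also mentioned.

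The Sample size section is built on a plain two-group comparison. "Intervention and control groups, estimated at 56 participants each", are said to give 80% power for an effect size of 0.57, "with a two-sided 5% significance level between the two group on depression scores". It gives no standard deviation and no correlation between visits, and does not say whether 0.57 refers to the 12-month score or to the change.

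PHQ-9 is collected at screening and at all follow-up research visits (PHQ-9 section). These fall one month after education and at 6 and 12 months (Follow-up visits). The last sentence of the main Analysis paragraph names baseline, post-education and 12-month data.

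**The concern.** The sample size, the primary outcome and the test do not line up. The sample size is for a single two-group difference, the outcome is a change to one time point, and the method is a repeated-measures ANOVA. With more than two visits, the group-by-time term of that ANOVA is an omnibus test spread over all of them. With baseline and 12 months only, it reduces to a comparison of raw change scores. Baseline PHQ-9 is in hand but enters as one more outcome level rather than as a covariate, so its information is used less well than it could be.

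A separate matter is pre-specification. If covariates and interactions are settled only after the models have been checked, the primary model is not fixed in advance. This bears on how far the primary result can be trusted, not on power.

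At stake are power in a trial of 150 and a clear primary result for Aim 2.

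**Working it through.** **Inputs from the protocol.** Effect size 0.57, two-sided 5%, 80% power, 56 evaluable per arm, 25% attrition, 150 randomised (75 per arm if equal), cited 12-month attrition of 6–18%.

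**Assumptions, not in the protocol.** Baseline-to-12-month correlation rho of 0.3, 0.4 or 0.5; 0.57 standardised on the 12-month SD; equal variances and equal correlation between visits; complete data in those analysed.

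**Step 1: the plan's own figure.** For d = 0.57 at 80% power, a two-sample comparison needs 49 per arm (normal) or 50 (t), not 56. With 56 per arm the power is about 85%. On attrition, 56/(1 − 0.25) = 74.7, or 75 per arm and 150 in all, which matches the number randomised; the stated 70 is 56 × 1.25. So the plan has some slack, which the figures below already include.

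**Step 2: change score against baseline adjustment.** In units of the 12-month variance, the change score has variance 2(1 − rho) and the baseline-adjusted score 1 − rho². The ratio is (1 − rho²)/[2(1 − rho)] = (1 + rho)/2, that is 0.65, 0.70 and 0.75 at rho 0.3, 0.4 and 0.5. It is below 1 whenever rho is below 1.

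Effective sizes:
- Change: 0.57/√[2(1 − rho)] = 0.482, 0.520, 0.570.
- Adjusted: 0.57/√(1 − rho²) = 0.598, 0.622, 0.658.

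**Step 3: omnibus group-by-time test.** Take four visits (baseline, 1, 6 and 12 months) with standardised differences 0, 0.19, 0.38 and 0.57. Their mean is 0.285 and the squared deviations sum to 0.1805. The noncentrality is (56/2) × 0.1805/(1 − rho) = 7.22, 8.42 and 10.11, on 3 and 330 degrees of freedom.

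**Power at 56 per arm (noncentral t and F):**

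| Test | rho 0.3 | rho 0.4 | rho 0.5 |
|---|---|---|---|
| 12-month contrast adjusted for baseline | 88% | 90% | 93% |
| Change score (group-by-time, two time points) | 72% | 78% | 85% |
| Group-by-time, four visits, gradual effect | 60% | 67% | 76% |

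**Step 4: sensitivity.**
- At rho 0.7 the three tests give 99%, 97% and 94%.
- The change score reaches 80% at rho of about 0.43.
- With 18% attrition (75 × 0.82 = 61.5 per arm) the change score gives about 76/82/88% at rho 0.3/0.4/0.5. With 6% (70.5 per arm) it gives about 81/87/92%.
- With three visits and an effect only at 12 months, the omnibus test gives about 75% at rho 0.3 and 88% at rho 0.5.
- If 0.57 is already on the change scale, the change comparison has about 85% power at 56 per arm whatever rho is.

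**The case against.** The strongest reply is that the shortfall is assumed rather than shown. The protocol does not give rho, does not say on which scale 0.57 is expressed, and calls its 25% attrition cautious. Step 4 shows how much turns on these points, so a reader who infers that the trial is underpowered goes further than the documents allow. This objection stands. It does not touch the efficiency comparison in Step 2, which holds at every rho below 1.

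Four stronger readings should also be set aside.
- *No test answers the 12-month question.* The Aim 2 text names the 12-month change and compares the arms on it. With two time points the group-by-time term is exactly that comparison.
- *The group main effect, which averages in baseline, is the deciding test.* The protocol does not say so, and the Aim 1 text, which speaks of differences between arms over time, points to group-by-time.
- *The responder proportion replaces the mean.* The change is labelled primary; the 5-point proportion is an added hypothesis. Its power depends on rho and on a control response rate that the protocol does not give.
- *The 5% error rate is uncontrolled because covariates are picked from baseline significance tests.* The text does not link the two steps, and no inflation can be calculated from it. What remains is that the covariate set is open.

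It can also be said that the covariance structure and the exact contrast belong in a statistical analysis plan, which is not shown. That is fair for the detail. But the article does not leave the method blank: it states ANOVA and a check for further covariates, and those statements are what should change.

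**Conclusion.** The point holds as one of efficiency and pre-specification, not as a demonstrated power failure. For the stated primary outcome of Aim 2, the stated method is less powerful than a baseline-adjusted 12-month contrast. Under the assumptions above, at 56 per arm and rho 0.3 to 0.5, the adjusted contrast gains about 8 to 16 percentage points over the change score (93 − 85 and 88 − 72) and about 17 to 28 over the four-visit omnibus test (93 − 76 and 88 − 60). Power below 80% is possible at low to moderate rho; it is avoided with higher rho, with sufficiently lower attrition, or if 0.57 refers to the change. The open covariate step is a separate weakness with no calculable size. The change should be made, but the trial is not invalid without it.

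**What to change.** In the Analysis section, including its Aim 2 text:
- Make the primary Aim 2 test the MBIC + DEF minus MBIC + SE difference in PHQ-9 at 12 months, adjusted for baseline PHQ-9, from a mixed model using all available visits (or from ANCOVA at 12 months). The mixed model also suits the stated aim of using all available data, because a conventional repeated-measures ANOVA drops anyone with a missing visit.
- Use the same form for the DKM and the three stigma scales, each with its own baseline.
- Replace the check for further covariates and interactions with a list named before data lock, and do not choose it from the baseline significance tests.
- Label the 5-point and 50% responder results as supportive.

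The cost is analysis wording only. Baseline values are already collected, no visit or participant is added, and the Trial status section puts data lock at January 2019, so the wording can be settled before then.
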